## Protocol

### Study objectives and hypotheses

*Overall hypothesis*

Wasting malnutrition at any age has medium- and long-term detrimental effects on endocrine and exocrine pancreatic function and structure.
1.
**
*Specific objective 1*:** To investigate whether wasting malnutrition at various ages is associated with abnormalities of pancreas structure and function later in life.a.
**
*Hypothesis 1*:** Prior wasting malnutrition is associated with later abnormal pancreatic structure and endocrine and exocrine function.b.
**
*Pancreatic phenotype of interest:*
** Diabetes assessed by oral glucose tolerance test (OGTT) and haemoglobin A1c (HbA1c), exocrine pancreatic function tests (serum lipase, faecal elastase), pancreatic size and architecture measured using ultrasound for all participants and measured using computed tomography (CT) scans for a subset of participants (non-pregnant adult participants).2.
**
*Specific objective 2:*
** To investigate whether pancreatic abnormalities in participants with prior malnutrition and diabetes are analogous to a previously described entity of fibro-calculous diabetes.a.
**
*Hypothesis 2:*
** Prior wasting malnutrition is associated with pancreatic calcification which in turn is associated with diabetes.b.
**
*Pancreatic phenotype of interest:*
** Pancreatic calcifications determined from CT scans among non-pregnant adult study participants.3.
**
*Specific objective 3:*
** To investigate the relative importance of decreased insulin production or increased insulin resistance in malnutrition-associated diabetes.a.
**
*Hypothesis 3:*
** The abnormal glucose regulation seen after wasting malnutrition is associated with relative insulin deficiency with or without insulin resistance.b.
**
*Pancreatic phenotype of interest:*
** Indices of glucose metabolism and insulin kinetics based on mathematical models of glucose and hormone concentrations during OGTT and intravenous glucose tolerance tests (IVGTT). Homeostasis model assessment of insulin resistance (HOMA-IR) and liver fat (insulin resistance) will also be assessed.4.
**
*Specific objective 4:*
** To investigate whether a prior abnormal pro-insulin/insulin ratio is associated with diabetes in adults infected or not with HIV or previously with tuberculosis.a.
**
*Hypothesis 4:*
** An abnormal pro-insulin/insulin ratio is associated with later development of diabetes in adults who had malnutrition earlier in life in association with HIV or tuberculosis infection.b.
**

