**3.**	** *CICADA (Chronic Infections, Co-morbidities and Diabetes in Africa), Mwanza, Tanzania* ** The CICADA cohort, ^ 17 ^ total n=1947, comprises three subgroups: a) Tuberculosis patients and controls from the TB-NUT study whose HIV and nutritional status ~16 years ago at recruitment are known (50% BMI<18.5 kg/m ^2^) as well as more recently recruited HIV-infected and uninfected people (controls) ^ 18 ^ ^,^ ^ 19 ^ b) NUSTART, conducted 2010-2014, was a two-site (Mwanza and Lusaka) trial of food supplements for malnourished (BMI<18.5 kg/m ^2^) HIV-infected adults, recruited when starting antiretroviral therapy. ^ 20 ^ In Mwanza, 704 participants were recruited, 409 were alive and followed at the 12-week NUSTART end-point; 273 were available at a follow-up two-three years after starting ART and 206 were recruited to the CICADA study. c) HIV-infected and uninfected people, both malnourished and well-nourished, recruited 3-four years ago for HIV, nutrition and diabetes assessments *CICADA has the most detailed longitudinal diabetes data of the project cohorts, archived fasting samples, and are the oldest so have had longer to develop diabetes; therefore, this cohort will be used for the in-depth and longitudinal components.*	CICADA (TB-NUT) 16 y prior: 450 total • 73 (16.2%) BMI <17 kg/m ^2^ • 74 (16.4%) BMI 17 to 18.5 kg/m ^2^ • 303 (67.4%) BMI > 18.5 kg/m ^2^ CICADA (NUSTART) 11 y prior: 208 total • 105 (50.5%) BMI <17 kg/m ^2^ • 103 (49.5 %) BMI 17 to 18.5 kg/m ^2^ CICADA (New HIV +/- cohort) 4 y prior: 1293 total • 109 (8.4%) BMI <17 kg/m ^2^ • 171 (13.3 %) BMI 17 to 18.5 kg/m ^2^ • 1009 (78.3%) BMI >18.5 kg/m ^2^ Expected for SAMPA: 1412 total
**4.**	** *NUSTART, Lusaka, Zambia* ** 200 previously malnourished HIV-infected adults will be traced and recruited from the NUSTART Lusaka participants. ^ 20 ^ We will also recruit 50 HIV-infected and 50 non-HIV-infected, not previously malnourished, neighbourhood controls.	• 10 y prior: 1111 total, 437 (39%) BMI 17 to 18.5 kg/m ^2^, 674 (61%) BMI<17 kg/m ^2^ • Expected for SAMPA: 300 total

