*Anthropometry*:** Anthropometry will use standard methods
^
27
^ conducted by trained staff. At each site technical error of measurement will be assessed and further training provided so that all staff reach acceptable levels of agreement with the local criterion anthropometrist.
^
28
^ Anthropometric measurements will be weight, height, sitting height, tibia length, circumferences of waist, hip and mid-upper arm, and triceps and subscapular skinfold thicknesses.7.
**
*Body composition:*
** All sites will use bioelectrical impedance (BIA) for body composition assessment. Lusaka will additionally use air displacement plethysmography (BodPod) and can assess its agreement with BIA.

The following assessments will be conducted in only subsets of consenting participants.
8.
**
*Detailed OGTT*
**: The same OGTT protocol will be used as above but, for 80 participants in each of the CICADA and St-ATT cohorts, referred to as the in-depth subset, we will measure additional hormones: glucagon, gastric inhibitory peptide (GIP), glucagon-like peptide-1 (GLP-1) at multiple time points and trypsinogen in baseline samples. The in-depth subsets will be randomly selected from the cohort participants, stratified by whether or not they were recorded as previously malnourished in our databases from earlier follow-ups. In event of refusals, replacements will be from the next in the randomised lists.9.
**
*IVGTT:*
** This test is the gold standard for estimating the early insulin response. It will be done only in the in-depth subset from CICADA. Results will be compared with OGTT in the same participants in order to better understand the OGTT results. For this test a solution of sterile 50% dextrose, in amounts 0.3 g/kg body weight, will be injected into the antecubital vein over 60 seconds starting at time 0 minutes. Blood samples will be taken at -10, -1, 2, 4, 6, 8, 10 minutes for measurement of glucose, insulin, C-peptide and glucagon.10.
**
*CT scans*
**: The CT studies will be performed in 100 participants from each of the adult cohorts by qualified and experienced radiologists in identified health facilities. Participants will be randomly selected, similarly to the in-depth subsets. Scans will be taken without use of contrast agents. The protocol will assess the following:•Pancreatic volume (in cm

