### Statistical analyses and sample size calculations

Analyses related to individual hypotheses are described below. Primary analyses will be conducted for each cohort separately. Pooled analyses using all or some cohorts combined will be conducted based on the individual cohort results, and in order to investigate how age at malnutrition and length of time between malnutrition and outcome assessment influence the associations between malnutrition and pancreas structure and function. Analyses will be guided by the conceptual framework in
Figure 1. Sample sizes for the specific hypotheses indicate that, with the available number of participants in the cohorts, we have sufficient power for the main analyses with all participants. For some expensive or labour- and participant-intensive outcomes, we had to consider cost and feasibility and have calculated power for analyses in subsets.

*Hypothesis 1:*
Prior malnutrition is associated with later abnormal pancreatic structure and endocrine and exocrine function.

Participants with and without prior wasting malnutrition, the SAMPA study primary exposure, will be compared within each cohort for all pancreas structure and function outcomes: diabetes by OGTT or HbA1c, exocrine function as indicated by faecal elastase and serum lipase, and pancreas size and presence of abnormalities detected by ultrasound or CT scan. We will initially fit regression models for each outcome with prior malnutrition as the main exposure, controlling for sex and for age as a continuous variable. We will investigate whether there are interactions between prior malnutrition and sex, which is known to be associated with both prior malnutrition and diabetes. We will then investigate whether the associations between malnutrition and the outcomes differ by the following variables:
•Time since malnutrition•Sitting/standing height ratio as an indicator of early life stunting•HIV status for African cohorts only (SAM Lusaka, NUSTART Lusaka, CICADA)

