*i.e.* glucose, hormones, faecal elastase and serum lipase, the available sample size in the smallest cohort will be sufficient to determine differences of 0.4 times the standard deviation with 90% power. Expected differences in pancreas volume were calculated using volume normalised to kg body weight to account for the participant age and size range.
^
35
^ A total of n=100 per cohort (assuming a standard deviation of 0.3 mL/kg) will provide 90% power to detect differences of 0.2 mL/kg between those with/without prior malnutrition, which is a smaller difference than that expected between people with and without diabetes.
^
35
^
^,^
^
36
^

*Hypothesis 2:*
Prior malnutrition is associated with pancreatic calcification which in turn is associated with diabetes.

To investigate whether prior malnutrition is associated with pancreas calcification, from each adult cohort we will randomly select for CT scans 50 participants who were exposed to malnutrition and 50 controls who were not exposed. The presence of calcification or other pancreas abnormalities on CT will be compared between those with or without prior malnutrition.

In order to increase sample size for this and for the second part of the hypothesis comparing calcification with diabetes, results from CT scans in the subset of participants with these will be compared with the ultrasound results from the same participants to indicate whether abnormalities determined by ultrasound, e.g. pancreas body or duct shape, correspond to calcification by CT scan. We will then compare the proportion of abnormalities based on ultrasound or CT scan among those with and without diabetes.

**
*Sample size*
**: Population prevalence estimates for pancreatic calcification appear unavailable so we have not performed any sample size calculations. Pancreatic calcifications are seen in fibro-calculous pancreatic diabetes
^
7
^ but these studies have been conducted on participants selected for their clinical presentation.

*Hypothesis 3:*
The abnormal glucose regulation seen after malnutrition is associated with relative insulin deficiency with or without insulin resistance.

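### Abnormality by ultrasound or CT is not confined to one test per comparison, while CT coverage differs about twofold by prior malnutrition in three of the four adult cohorts and in opposite directions

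*Protocol article*

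**What the plan says.** Under Study objectives and hypotheses, pancreas size and architecture are "measured using ultrasound for all participants and measured using computed tomography (CT) scans for a subset of participants". Under Assessments, "The CT studies will be performed in 100 participants from each of the adult cohorts". The Hypothesis 2 text fixes the split: "from each adult cohort we will randomly select for CT scans 50 participants who were exposed to malnutrition and 50 controls who were not exposed".

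Three imaging comparisons are then stated in the statistical section of the protocol article:

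- Hypothesis 1, by prior malnutrition within each cohort: the listed outcomes include "pancreas size and presence of abnormalities detected by ultrasound or CT scan".
- Hypothesis 2, by prior malnutrition, CT only: "The presence of calcification or other pancreas abnormalities on CT will be compared between those with or without prior malnutrition".
- Hypothesis 2, by diabetes: "We will then compare the proportion of abnormalities based on ultrasound or CT scan among those with and without diabetes". This follows a step that checks ultrasound against CT in participants who had both. Its declared purpose is a larger sample for the malnutrition contrast as well as for the diabetes contrast.

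The Hypothesis 1 regressions start with sex and age as covariates. Having had a CT is not mentioned as a covariate, stratum or weight.

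**The concern.** CT numbers are fixed at 50 and 50, but the exposure groups they are drawn from are unequal. The chance that a participant has a second, probably more sensitive, test therefore depends on exposure group. If a participant counts as abnormal when either test is positive, the group with more CT will show more abnormalities even when the truth is the same in both.

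The direction is not constant. In NUSTART Lusaka the comparators are the smaller group and are scanned more. In CLHNS and CICADA the malnourished are the smaller group and are scanned more. The article plans pooled analyses to learn how age at malnutrition changes the associations. CLHNS malnutrition was recorded by age two and NUSTART malnutrition in adulthood, so artefacts of opposite sign in these two cohorts could pass for modification by age.

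**Working it through.** **The plan's own figure for the CT subset.** The article gives 90% power for a pancreas volume difference of 0.2 mL/kg, SD 0.3, with 100 scans per cohort. With 50 v 50 and two-sided alpha 0.05 (assumed), the standardised difference is 0.2 / (0.3 × √(2/50)) = 0.2 / 0.06 = 3.33. Then 3.33 − 1.96 = 1.37, which is power of about 91.5%. The figure reproduces, and the balanced CT subset is adequate for volume. Hypothesis 2 itself has no sample size calculation to check.

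**Group sizes, from Table 1.**

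- NUSTART Lusaka: 200 malnourished. For comparators, "We will also recruit 50 HIV-infected and 50 non-HIV-infected, not previously malnourished, neighbourhood controls", so 100.
- CLHNS: 143 malnourished of 420, leaving 277.
- CICADA: (73 + 74 + 105 + 103 + 109 + 171) / (450 + 208 + 1293) = 635 / 1951 = 32.5% with BMI below 18.5. Applied to the 1412 expected, about 460 and 952.
- St-ATT: 21% + 24% = 45% with BMI below 18.5. Applied to the 600 expected, 270 and 330.

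The first two are planned numbers. The last two assume that the Table 1 shares persist among those who return and that exposure means BMI below 18.5.

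**CT coverage, f = 50 / group size.**

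| Cohort | Malnourished | Comparator | Ratio |
|---|---|---|---|
| NUSTART Lusaka | 50/200 = 25.0% | 50/100 = 50.0% | 0.50 |
| CLHNS | 50/143 = 35.0% | 50/277 = 18.1% | 1.94 |
| CICADA | 50/460 = 10.9% | 50/952 = 5.3% | 2.07 |
| St-ATT | 50/270 = 18.5% | 50/330 = 15.2% | 1.22 |

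If exposure were instead BMI below 17, coverage would be 24.1% v 4.2% in CICADA and 34.7% v 11.0% in St-ATT.

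**Effect on a merged outcome.** Assumptions not in the document: equal true prevalence in both groups, CT sensitivity 0.95, no false positives, independent tests, ultrasound sensitivity s. The probability of detecting a true abnormality is

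D(f) = f × [1 − (1 − 0.95)(1 − s)] + (1 − f) × s = s + 0.95 × f × (1 − s).

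Example for NUSTART with s = 0.50: malnourished 0.50 + 0.95 × 0.25 × 0.50 = 0.619; comparators 0.50 + 0.95 × 0.50 × 0.50 = 0.738; ratio 0.84. True prevalence cancels from the ratio.

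| Cohort | s = 0.25 | s = 0.50 | s = 0.75 |
|---|---|---|---|
| NUSTART Lusaka | 0.71 | 0.84 | 0.93 |
| CLHNS | 1.32 | 1.14 | 1.05 |
| CICADA | 1.14 | 1.05 | 1.02 |
| St-ATT | 1.07 | 1.03 | 1.01 |

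Between CLHNS and NUSTART the artefacts differ by a factor of 1.14 / 0.84 = 1.36 at s = 0.50.

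**The diabetes contrast.** Take the article's Hypothesis 1 planning figures: hyperglycaemia in 7% of the unexposed and 7% + 7.5% = 14.5% of the exposed. In NUSTART this gives 29 exposed and 7 unexposed cases. Their expected scans are 29 × 0.25 + 7 × 0.50 = 10.75 of 36, or 29.9%. Among non-cases it is (171 × 0.25 + 93 × 0.50) / 264 = 33.8%. The same steps give 26.8% v 23.5% in CLHNS, 8.1% v 7.0% in CICADA and 17.3% v 16.6% in St-ATT. With s = 0.50 the spurious ratios are 0.97, 1.03, 1.01 and 1.01 respectively.

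**The case against.** The strongest reply is that the article never defines an either-positive outcome. In the Hypothesis 1 list, size and abnormalities share one phrase, and size cannot be an either-positive composite. Models are to be fitted outcome by outcome, calcification is defined on CT alone, and a balanced 50 v 50 CT comparison by malnutrition is already planned. The ultrasound step can be read as testing whether ultrasound may stand in for CT, and since everyone has ultrasound that use creates no unequal coverage. Article-level text also commonly leaves the coding of two imaging tests to a fuller document.

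Much of this stands. Separate analysis is a legitimate reading, and the 50 v 50 comparison is free of the problem. It does not settle the matter, because the stated aim is to go beyond the CT subset for both contrasts and the outcome then named is a single proportion resting on either test. That is an ambiguity in stated text, not merely absent detail.

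Three stronger readings are not supported:

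- A reader might infer that the plan definitely merges the tests. The wording allows this but does not say it.
- A reader might infer from the sentence on diabetes that the diabetes result would be seriously distorted. On the article's own planning prevalences it would hardly move.
- A reader might infer that every adult cohort is scanned very unevenly. St-ATT is nearly balanced at the BMI 18.5 cut-off.

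**Conclusion.** The point holds conditionally. Fixed 50/50 CT sampling gives roughly twofold different coverage by malnutrition status in NUSTART Lusaka and CLHNS on the document's own numbers, and in CICADA if the Table 1 shares persist, with the direction reversed in NUSTART. If the two tests are merged, the malnutrition comparison of abnormalities is biased with no true effect, downward in NUSTART and upward in CLHNS, by the amounts tabulated above.

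The size rests on assumed sensitivities and shrinks towards nothing as ultrasound approaches CT in sensitivity. Pancreatic structure and calcification are secondary outcomes, and the primary endocrine and exocrine outcomes are untouched. The ambiguity should be closed before analysis.

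**What to change.** In the Hypothesis 1 and Hypothesis 2 analysis text, state that:

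- full-cohort comparisons of abnormalities, by malnutrition and by diabetes, use the ultrasound result alone for every participant, including those who also had CT;
- CT results are analysed only within the CT subset, as in the 50 v 50 comparison already planned, and to assess how well ultrasound agrees with CT;
- no either-test outcome is formed across scanned and unscanned participants.

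With one test per comparison, the difference in detection by malnutrition status that comes from unequal CT coverage is zero in every cohort. The cost is wording only, with no change to scans or recruitment. The drawback is that abnormalities seen only on CT do not count in the full-cohort proportion, which will be somewhat lower. If separate analysis was always intended, the same sentences simply make that explicit.

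### The second part of Hypothesis 2 is about calcification and diabetes, but the stated comparison uses unrestricted ultrasound or CT abnormalities and can be positive through non-calcific findings

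*Protocol article*

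**What the plan says.** Under Study objectives and hypotheses, Hypothesis 2 reads: "Prior wasting malnutrition is associated with pancreatic calcification which in turn is associated with diabetes". The only phenotype named for that objective is "Pancreatic calcifications determined from CT scans among non-pregnant adult study participants". Outcome measures keeps the same separation: CT calcification is secondary outcome 2, and pancreas size and architecture is secondary outcome 1.

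Under Statistical analyses and sample size calculations, Hypothesis 2 is handled in three steps.

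- For malnutrition and calcification, 50 exposed and 50 unexposed participants per adult cohort have CT, and "The presence of calcification or other pancreas abnormalities on CT will be compared between those with or without prior malnutrition".
- A linking step is added, with the purpose "In order to increase sample size for this and for the second part of the hypothesis comparing calcification with diabetes". CT and ultrasound results from the same participants are compared "to indicate whether abnormalities determined by ultrasound, e.g. pancreas body or duct shape, correspond to calcification by CT scan".
- For calcification and diabetes: "We will then compare the proportion of abnormalities based on ultrasound or CT scan among those with and without diabetes".

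No sample size is calculated for this hypothesis, because the protocol found no population prevalence for calcification.

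**The concern.** The null hypothesis implied by the objective is that calcification and diabetes are unrelated. The null hypothesis that the last step tests is that abnormalities seen on ultrasound or CT, of whatever kind, are unrelated to diabetes. Rejecting the second does not reject the first.

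The linking step narrows this gap in intention but not in the text. It gives no level of agreement, does not confine the diabetes comparison to the signs found to agree, and does not say what follows if they do not agree.

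Objective 2 asks whether the pancreatic abnormalities resemble a fibro-calculous entity. A positive result made up mainly of duct or body-shape findings would not answer that, but under the present wording it could be read as support for it.

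**Working it through.** **Stated figure.** The protocol gives no power or prevalence for Hypothesis 2, so there is nothing to reproduce. What follows only illustrates the mechanism.

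**Inputs from the protocol.** Expected CICADA size 1412 and St-ATT size 600 (Table 1); 100 CT scans in each of four adult cohorts, so 4 × 100 = 400 (Assessments).

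**Assumptions.** Calcification prevalence c is the same with and without diabetes. Other abnormalities have prevalence o, independent of calcification. Diabetes affects 5%, 7% or 11% of participants. The 7% and 11% are borrowed from the protocol's figures for hyperglycaemia in people without prior malnutrition, which is a wider category than diabetes. Tests are two-sided at 5%; the protocol states no alpha.

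**Formulas.** Prevalence of any abnormality: p = 1 − (1 − c)(1 − o). Rejection probability ≈ Φ[(|p1 − p0| − 1.96 × SE0) / SE1], where SE0 uses the pooled proportion and SE1 the separate proportions.

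**One setting in full.** n = 1412, 5% diabetes, c = 2%, o = 10% without and 20% with diabetes.

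- Groups: 0.05 × 1412 = 70.6 with diabetes and 1341.4 without.
- p0 = 1 − 0.98 × 0.90 = 0.118; p1 = 1 − 0.98 × 0.80 = 0.216; difference 0.098.
- Pooled p = (70.6 × 0.216 + 1341.4 × 0.118) / 1412 = 0.1229.
- SE0 = √[0.1229 × 0.8771 × (1/70.6 + 1/1341.4)] = 0.0401.
- SE1 = √[0.216 × 0.784/70.6 + 0.118 × 0.882/1341.4] = 0.0498.
- Φ[(0.098 − 1.96 × 0.0401)/0.0498] = Φ(0.39) ≈ 0.65.

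A simulation of the same setting (1500 runs, chi-square test) gave 66%.

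**Range of results, calcification unrelated to diabetes throughout**

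| Other abnormalities, without v with diabetes | n = 1412, c = 2%, diabetes 5% (simulated) | n = 1412, c = 3%, diabetes 7% to 11% (formula) | n = 600, c = 3%, diabetes 7% to 11% (formula) |
|---|---|---|---|
| 10% v 10% | not run; nominal 5% | 5% | 5% |
| 10% v 15% | 24% | 30% to 40% | 17% to 22% |
| 10% v 20% | 66% | 74% to 87% | 44% to 57% |

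A calcification-only Fisher test in the simulations at n = 1412 rejected in about 2% to 3% of runs, as it should when there is no link.

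**What the abnormal group contains.** In the worked setting, calcified participants make up 0.02/0.1229 = 16% of those counted as abnormal.

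**What the linking step can show.** If ultrasound flags all k calcified cases, the exact lower 95% limit for its sensitivity is 0.025^(1/k).

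| Assumed calcification | Cases in 100 scans (lower limit) | Cases in 400 scans (lower limit) |
|---|---|---|
| 1% | 1 (2.5%) | 4 (40%) |
| 3% | 3 (29%) | 12 (74%) |
| 5% | 5 (48%) | 20 (83%) |

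Even perfect observed detection leaves wide uncertainty within a cohort, and the protocol makes analysis by cohort primary.

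**The case against.** The strongest defence is to read the paragraph in sequence. Its declared aim is a larger sample for comparing calcification with diabetes, and the check of ultrasound against CT comes before the diabetes comparison. On that reading the abnormalities in the last step are the ultrasound signs validated as a proxy, and the agreement threshold and fallback are details for a fuller document. This stands as a plausible account of the intention. It does not settle the point, because the sentence that fixes the comparison carries no such restriction, and no comparison of CT calcification itself by diabetes status is stated.

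A reader might go further and infer that the test will reject because pancreas size differs by diabetes status. The protocol does expect a volume difference: its Hypothesis 1 power statement for 0.2 mL/kg adds "which is a smaller difference than that expected between people with and without diabetes". But the Hypothesis 1 analysis lists size apart from abnormalities, the examples under Hypothesis 2 are body and duct shape, and nowhere is a small pancreas defined as abnormal. Nor do the documents show that non-calcific abnormalities differ by diabetes status. If they do not, rejection stays near 5%. So the supported statement is that the test can reject, not that it will.

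The malnutrition comparison on CT is also open to two readings: calcification and other abnormalities as two items, or as one combined outcome. It needs clarifying, but it is not shown to be a composite.

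Finally, an ultrasound-based supporting analysis meets the same scarcity of calcified cases as the linking step. That is true, and is why it should only support.

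**Conclusion.** The point holds in a limited form. The outcome compared by diabetes status is broader than the hypothesis, and the plan neither confines it to calcification or a validated proxy nor states the direct comparison. A positive result would therefore not by itself show a link between calcification and diabetes.

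The size cannot be fixed from the documents. The illustrative span at n = 1412 runs from about 5% to about 87%, governed almost entirely by the assumed difference in non-calcific abnormalities. These figures show that the mechanism can matter; they do not forecast the result. The change is worth making because it costs little and settles what Hypothesis 2 tests.

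**What to change.** - State calcification on CT as the outcome for both parts of Hypothesis 2: by prior malnutrition and by diabetes status.
- As a supporting analysis in all adults, use ultrasound-recorded calcification, or only those ultrasound signs shown to agree with CT calcification. Set the agreement criterion beforehand and say what happens if it is not met.
- Report ultrasound sensitivity and specificity against CT with confidence intervals, and note that few calcified cases will make them imprecise.
- Report duct, shape and other abnormalities separately under Hypothesis 1, and do not count them as evidence on calcification.

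No new data are needed, since calcification is already recorded on both CT and ultrasound (Assessments). The cost is fewer events and wider intervals than the broader comparison would give, and the CT result may be inconclusive if calcification is rare.

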A deeper understanding of associations between prior malnutrition and the underlying glucose metabolic pathways will be explored through modelling biochemical measures over the course of the two-hour OGTT. Glucose, insulin and C-peptide data from OGTT will be used to model pancreatic cell functionality according to published methods in order to determine a set of indices quantifying: first phase, second phase, and total insulin secretion,
^
37
^ whole-body and hepatic insulin clearance,
^
38
^ and insulin sensitivity.
^
25
^
^,^
^
39
^ For the child cohorts for whom only three blood samples are available over the two-hour OGTT, we will use methods designed to determine insulin sensitivity from sparsely sampled OGTTs.
^
26
^ The IVGTT data from the CICADA cohort subset can be similarly modelled to estimate insulin sensitivity and insulin secretion. Comparison of the indices estimated from the two tests will provide information as to whether altered intestinal function,
*e.g.* glucose absorption or incretin secretion, influences insulin secretion or sensitivity in participants previously malnourished or not.

**
*Sample size*
**: We will use individual data from all SAMPA adult participants and, for children who have only three sample points during OGTT, we will combine data from groups of participants.
^
26
^ Most previous studies in this area include 10-100 people per group, whereas we will be able to study all SAMPA participants.

*Hypothesis 4:*
An abnormal fasting pro-insulin/insulin ratio is associated with later development of diabetes in adults who had malnutrition and infection.

**
*Analysis*
**: We will use the detailed data and samples available from CICADA to investigate whether the proinsulin/insulin ratio in CICADA samples collected from fasted participants about four years prior to the SAMPA visit is associated with diabetes or prediabetes at the SAMPA visit. This will be a nested case-control study where cases are 60 CICADA participants with current diabetes by OGTT and controls are 60 CICADA participants with normal OGTT. These participants will be selected by stratified random sampling. Logistic regression will be used, controlling for age and sex, to determine if prior proinsulin/insulin ratio is associated with later diabetes.

**
*Sample size*

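### The second link of Hypothesis 2 (calcification to diabetes) is to be tested by comparing proportions without conditioning on prior malnutrition, age or sex, so it can show an association that prior malnutrition alone produces

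*Protocol article*

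**What the plan says.** Under Study objectives and hypotheses, Hypothesis 2 is a two-step chain: "Prior wasting malnutrition is associated with pancreatic calcification which in turn is associated with diabetes". Under Statistical analyses and sample size calculations, the first step is examined by CT in 50 exposed and 50 unexposed participants from each adult cohort. To gain sample size, ultrasound findings are then checked against CT in the participants who have both. The second step is to "compare the proportion of abnormalities based on ultrasound or CT scan among those with and without diabetes". No model, covariate or stratifier is named, and no sample size is calculated for this hypothesis.

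Elsewhere in the same section adjustment is named. The Hypothesis 1 models are fitted "with prior malnutrition as the main exposure, controlling for sex and for age as a continuous variable". For Hypothesis 4, "Logistic regression will be used, controlling for age and sex". Neither sentence reaches the comparison of abnormality with diabetes: the exposure is prior malnutrition in the first and the proinsulin/insulin ratio in the second. The introduction to the section, which covers all four hypotheses, also says: "Primary analyses will be conducted for each cohort separately".

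**The concern.** The second step of the chain is informative only if calcification is related to diabetes among people with the same malnutrition history. A comparison of overall proportions tests something weaker, namely whether the two are associated at all. By the study's own premise they would be, even without a link between them. Hypothesis 1 reads "Prior malnutrition is associated with later abnormal pancreatic structure and endocrine and exocrine function", so malnutrition is expected to act on both variables. The article also describes "sex, which is known to be associated with both prior malnutrition and diabetes", and age is a further candidate common cause.

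At stake is the question in Specific objective 2, whether these participants have something like fibro-calculous diabetes. A crude difference cannot separate calcification lying on the path to diabetes from malnutrition producing each of them separately. Those two readings would support different accounts of the disease.

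**Working it through.** The article gives no power or error rate for Hypothesis 2, so there is no figure of its own to reproduce. The check asks how often a crude comparison would reject if abnormality and diabetes were independent within each malnutrition group.

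**Inputs from the article**
- Dysglycaemia (2-hour glucose of 7.8 mmol/L or more) in the unexposed: 7%. Difference used for power: 7.5 points, giving 14.5% in the exposed. Differences reported from earlier studies run from 3% to 9%. The check uses 3 points (7% v 10%) and 7.5 points (7% v 14.5%).
- CT subset: 50 exposed, 50 unexposed.
- St-ATT: 600 expected. Table 1 has 189 + 216 = 405 of 900 below BMI 18.5, which is 45%, or 270 exposed and 330 unexposed.
- CICADA: 1412 expected. Table 1 has 73 + 74 + 105 + 103 + 109 + 171 = 635 of 450 + 208 + 1293 = 1951, which is 32.5%, or about 460 exposed and 952 unexposed.

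**Assumptions**
- Abnormality prevalence, unexposed v exposed: 5% v 10%, 5% v 15%, 10% v 30%, 10% v 40%. The article says calcification prevalence is unavailable.
- Two-sided 5% level, Pearson chi-square for the crude comparison. Neither is stated in the article.
- BMI below 18.5 counts as prior malnutrition, and the expected participants keep the Table 1 proportions.

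**Crude odds ratio with no link within groups.** Write w for the share in each malnutrition group, d for the dysglycaemia rate and a for the abnormality rate. Each cell of the crude table is a sum over the two groups, for example P(abnormal and diabetic) = Σ w·d·a.

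CICADA, 10% v 40% and 7% v 14.5%, with w = 460/1412 = 0.3258 exposed and 0.6742 unexposed:
- abnormal, diabetic: 0.3258 × 0.145 × 0.40 + 0.6742 × 0.07 × 0.10 = 0.0236
- abnormal, not diabetic: 0.3258 × 0.855 × 0.40 + 0.6742 × 0.93 × 0.10 = 0.1741
- normal, diabetic: 0.3258 × 0.145 × 0.60 + 0.6742 × 0.07 × 0.90 = 0.0708
- normal, not diabetic: 0.3258 × 0.855 × 0.60 + 0.6742 × 0.93 × 0.90 = 0.7314

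Crude OR = (0.0236 × 0.7314) / (0.1741 × 0.0708) = 1.40, although the odds ratio within each malnutrition group is exactly 1.

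**Rejection rates** by simulation (at least 40,000 replicates per setting). Ranges run over the four abnormality assumptions:

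| Sample | Gap 3 points: crude OR | rejects | Gap 7.5 points: crude OR | rejects |
|---|---|---|---|---|
| One CT subset, 100 | 1.07–1.16 | 5%–6% | 1.14–1.34 | 6%–8% |
| St-ATT, 600 | 1.07–1.17 | 5.5%–8.5% | 1.15–1.37 | 7%–20% |
| CICADA, 1412 | 1.07–1.18 | 6%–12% | 1.16–1.40 | 8%–36% |

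A Cochran-Mantel-Haenszel test stratified by prior malnutrition rejects in about 4% to 5% throughout.

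**Age, as illustration only.** Take age as the sole common cause, with each sample split into younger and older halves, assumed diabetes of 5% v 15% or 4% v 20%, and abnormality of 5% v 15% or 10% v 30%. The crude test then rejects in 8%–12% (n = 100), 13%–34% (n = 600) and 20%–62% (n = 1412). Stratifying by age returns it to about 4%–5%. None of these age effects comes from the article.

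**The case against.** **The article condenses a fuller plan.** It never calls the comparison unadjusted and names no test. Under Hypothesis 1, a sentence about comparing groups is followed at once by regression with covariates, so comparing need not mean crude. This stands as a caution: crude is inferred from the absence of any covariate. It does not dispose of the point, because the article names its covariates for Hypotheses 1 and 4 and commits to a different kind of analysis here.

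**The hypothesis claims only association.** No mediation test or decision rule is announced, and Specific objective 2 can be read as a phenotyping question. That is fair as far as it goes. But the hypothesis is worded as a sequence, "Prior malnutrition is associated with pancreatic calcification which in turn is associated with diabetes", and a crude association is predicted by Hypothesis 1 whether or not the second step is true.

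**Cohort.** A reader might infer that cohorts are merged to gain sample size, so that cohort differences also confound the comparison. The article does not support this. Primary analyses are by cohort, and the gain in sample size comes from ultrasound. In one assumed set of differing cohort prevalences with no link within cohorts, separate cohort tests rejected in 3.9%–5.2%. Cohort matters only for later pooled analyses, for which no cohort term is stated.

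**Size.** A reader might also infer that confounding makes the test reject. It inflates the false rejection rate, and in a single CT subset only slightly. The 36% figure needs an assumed 10% v 40% contrast in abnormality.

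**Conclusion.** The point holds in limited form. As written, the only analysis given for the second step of Hypothesis 2 does not condition on the study's main exposure, nor on age or sex, and can therefore show an abnormality-diabetes association with no link given malnutrition. With malnutrition as the only common cause, the false rejection rate at a nominal 5% is about 5%–8% in one CT subset, 5%–20% in St-ATT and 6%–36% in CICADA, with crude odds ratios of 1.07 to 1.40. The bias is small in the CT subset alone. It becomes material when ultrasound extends the comparison to a whole cohort.

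These figures rest on the assumed abnormality rates and test level. They also use rates for diabetes and impaired glucose tolerance combined. Diabetes alone would be rarer, and the inflation from malnutrition probably smaller. Confounding by age would add to it if both conditions become more common with age, but the article does not allow that amount to be fixed. The 50:50 CT sampling sets the exposure mix in the CT data; no separate harm from it was shown. Since this is a secondary outcome and the fuller plan may already adjust, it is a change worth making and does not threaten the primary analyses.

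**What to change.** Replace the comparison of proportions with a logistic regression, within each cohort, of diabetes on abnormality or calcification, adjusted for prior malnutrition, age as a continuous variable, and sex. Add a cohort term only if cohorts are later pooled. State that any conclusion about the second step rests on the adjusted estimate. The crude proportions can still be shown as description.

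The change is a sentence or two in the analysis section and needs no new data. The price is precision: in the CT subset calcified or diabetic participants may be few, so a penalised (Firth) or exact stratified fit may be needed, and intervals will be wider than for the crude comparison.
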